## Abstract

In schizophrenia, social cognitive impairment is considered one of the greatest obstacles to social participation. Although numerous measures have been developed to assess social cognition, only a limited number of them have become available in Japan. We are therefore planning this evaluation study for social cognition measures in Japan (ESCoM) to confirm their psychometric characteristics and to promote research focused on social cognition. Participants in the cross-sectional observational study will be 140 patients with schizophrenia recruited from three Japanese facilities and 70 healthy individuals. In our primary analysis, we will calculate several psychometric indicators with a focus on whether they can independently predict social functioning. In secondary analyses, we will assess the reliability and validity of the Japanese translations of each measure and conduct an exploratory investigation of patient background, psychiatric symptoms, defeatist performance belief, and gut microbiota as determinants of social cognition. The protocol for this study is registered in UMIN-CTR, unique ID UMIN000043777.

## 1. Introduction

Schizophrenia is a severe mental disorder for which complete recovery is difficult to achieve by conventional therapies. As a result, patients with schizophrenia continue to have impaired social functioning. Although the prevalence of schizophrenia is a relatively low 1% [1], it is one of the top 15 causes of disability worldwide [2]. 

Social cognition is defined as “the mental operations that underlie social interactions, including perceiving, interpreting, and generating responses to the intentions, dispositions, and behaviors of others” [3]. In patients with schizophrenia or other mental disorders, social cognitive impairment is considered one of the greatest obstacles to social participation, such as interpersonal relationships, education, and employment [4].

Social cognition has become a major area of schizophrenia research, and the number of publications on this topic has increased remarkably in the past 20 years [3,5]. Measures for assessing social cognitive impairment have been developed from various perspectives. However, many of these measures are based on original theories, and reliability and validity have not been sufficiently examined for some of them [5]. To address this problem, the Social Cognition Psychometric Evaluation (SCOPE) study was conducted in the United States from 2012 to 2017. Through voting and discussion by an expert panel and two observational studies, six measures from a pool of 108 candidates were ultimately recommended for assessing social cognitive impairment in schizophrenia and other mental disorders [5,6,7]. The SCOPE study made significant advances in the assessment of social cognitive impairment, contributing a provisional test battery and serving as a foundation for future work. However, the results were based on data collected in only the United States, so the generalizability to other cultural contexts remains unclear. Notably, social cognition tasks are more sensitive than neurocognitive tasks to differences in language and culture [8]. 

In fact, there has been little effort to test the reliability and validity of the measures recommended by the SCOPE study in languages other than English or in cultural areas outside of the United States. A 2020 study of reliability and validity in Singapore by Lim et al. found that even among people who use English as a common language, reliability and validity results may differ by cultural area [9]. Going forward, as therapies are developed for social cognition, it will be absolutely paramount to examine the effects of cultural differences in the underlying assessments of social cognition. 

In Japan, some researchers have been working on developing a social cognition test battery for Japanese patients with schizophrenia [10], and validity studies have been conducted for social cognition measures such as the widely used Japanese versions of the Facial Emotion Selection Test (FEST) and Social Cognition Screening Questionnaire (SCSQ) [11,12]. However, reliability and validity have been assessed for only one of the Japanese versions of the six measures recommended by the SCOPE study. In addition, the reliability and validity of some social cognition measures currently used in Japan, including measures unique to Japan, have not been sufficiently assessed. Therefore, in order to prepare for future international clinical trials, it is necessary to assess not only the six measures recommended by the SCOPE study, but also the measures unique to Japan. 

Considering the above, we previously recruited a panel of Japanese experts on social cognition who discussed whether social cognition measures developed in the United States could be introduced in Japan, and the panel selected nine promising measures of social cognition in Japanese patients using a modified Delphi method [13]. Accordingly, the main objectives of the present study are to assess these measures selected by the domestic expert panel simultaneously in the same patients and to examine the relative merits of these social cognition measures by calculating psychometric indicators. Another objective is to hold an expert panel discussion of these psychometric indicators to produce recommendations on social cognition measures for Japanese patients.

To date, there have been studies examining cultural differences in social cognition measures between Asian and western countries [14] or attempting to establish new social cognition test batteries suited to their own specific study purposes [15,16]. However, this is the first study that will comprehensively evaluate the psychometric properties of social cognition measures in a non-English context using the framework of the SCOPE study. 

We will also examine clinical backgrounds, psychiatric symptoms, and defeatist performance belief as determinants of social cognition. Furthermore, based on the recent focus on the relation between the gut microbiome and schizophrenia [17], we will also measure gut microbiota in an exploratory investigation of social cognitive impairment, for which an effective treatment method has not yet been established. According to an experiment using germ-free mice, the gut microbiome plays an important role in cognition and social behavior [18]. When the gut microbiota of patients with schizophrenia were transplanted into germ-free mice, these animals demonstrated reduced functioning related to memory, learning, and social behavior compared with those receiving transplants of gut microbiota from healthy humans [19]. To date, five studies have been conducted on the gut microbiota in patients with schizophrenia. These studies have shown that the composition of the gut microbiota in patients is different from that in healthy individuals [20] and that gut microbiota composition is associated with symptoms of mental illness [21] and depression [22]. However, no study has yet examined the relation between social cognition and the gut microbiota in patients with schizophrenia. Therefore, in secondary analyses, we will assess the reliability and validity of the Japanese translations of the abovementioned measures and conduct an exploratory investigation of patient background, psychiatric symptoms, defeatist performance belief, and gut microbiota as determinants of social cognition. 

## 2. Methods and Analysis

### 2.1. Study Participants and Data Collection

This is a cross-sectional study. Patients with schizophrenia will be recruited from the National Center of Neurology and Psychiatry, Hokkaido University Hospital, and Toho University Omori Medical Center. Staff at each facility will screen patients based on their medical records and select eligible patients. Next, these patients will be examined by their attending physicians, who will confirm whether the patients meet the eligibility criteria. Healthy individuals will be recruited by methods such as flyers posted or distributed at the study facilities and e-mails about the study posted on mailing lists. Individuals who volunteer to participate will be interviewed by staff at the participating facilities, who will confirm the individuals’ eligibility. Individuals who meet the inclusion criteria will be given a written explanation of the study by staff at the participating facilities, who will then obtain written informed consent. The staff will assess measures with individuals who provide written consent. Anyone involved in the research agrees to participate and agrees to have details the results of the research about them published.

Of the nine tests recommended by the panel, the Penn Emotion Recognition Task (ER-40) [23] was excluded from the present study because a similar task, FEST, which measures cognitive functions related to facial expressions, is already available in Japanese. In addition, it requires the use of a unique interface and is difficult to administer compared with other measures in the same environment.

The study period for this cross-sectional study is from institutional review board (IRB) approval until 31 March 2023. Each measure will be conducted either once or twice. For healthy individuals, all assessments will be completed on the day that informed consent is obtained or within 1 week. For patients with schizophrenia, the initial assessment will be performed on the day that informed consent is obtained (day 0) or within 1 week (Table 1). In consideration of fatigue in participants, measures may be assessed over multiple days. In general, however, all measures are scheduled to be completed within several days.

### 2.2. Inclusion and Exclusion Criteria

Inclusion criteria for patients with schizophrenia are as follows: (1) primary diagnosis of schizophrenia based on the Diagnostic and Statistical Manual of Mental Disorders (DSM-5) at the time of assessment; (2) no hospitalization in the previous 2 months, no changes in prescriptions in the past 6 weeks, and no changes in prescription dosage in the past 2 weeks; (3) age 20−59 years at the time of obtaining informed consent; and (4) written informed consent to participate in the study based on an understanding of its objective and content (capacity to consent).

The inclusion criteria for healthy individuals are as follows: (1) age 20−59 years at the time of study participation; (2) confirmation of no diagnoses of mental disorders at the time of study participation; and (3) written informed consent to participate in the study.

For both patients with schizophrenia and healthy individuals, the exclusion criteria are as follows: (1) physical/mental disorders that prevent implementation of measures during study participation; (2) insufficient Japanese language ability to respond to self-reported psychological measures based on a sufficient understanding of the questions; and (3) being deemed ineligible to participate for any other reason by an attending physician or study staff.

### 2.3. Candidate Measures for Social Cognition

#### 2.3.1. Attributional Style Bias

Ambiguous Intentions and Hostility Questionnaire (AIHQ)The participant responds to questions about five situations with negative outcomes, such as questions on the cause of the situation, whether they feel the other person’s actions are intentional, and how they would respond to the situation. We obtained permission from the original authors to modify the existing Japanese version of the questionnaire by expanding the number of self-report items and removing rater-scored items, as suggested by Buck et al. [24]. The format was changed to address the limitations presented in the SCOPE study [5,6,7]. The estimated time required is 6 min [25].Intentionality Bias Task (IBT)The participant responds to 24 short sentences describing human actions within a time limit and indicates whether those actions are intentional or accidental. A Japanese version of the IBT was newly prepared for this study. The 24-question version used in the SCOPE study [7] was first translated into Japanese, and then back-translated to English for revision by the original author. In addition, modifications were made to the time conditions to account for differences in grammatical structure and average reading speed between English and Japanese. The estimated time required is 5 min [26].

#### 2.3.2. Emotion Processing

Bell Lysaker Emotion Recognition Task (BLERT)The participant views videos of actors and, using the actor’s facial expression, tone of voice, vocal timbre, and upper body movement as clues, responds to multiple-choice questions asking which emotion was being expressed. A new Japanese version, refilmed with a Japanese actor and a translated script, was prepared with permission from the original author. The estimated time required is 7 min [27].Facial Emotion Selection Test (FEST)The participant views photos of Japanese faces of different genders and ages and selects the emotion that most closely matches the expression in the photo from 7 choices (Ekman’s six basic emotions and emotionless). This test was created in Japan with reference to the Facial Emotion Identification Task (FEIT) [28]. The estimated time required is 10 min [11].

#### 2.3.3. Social Perception

Social Attribution Task-Multiple Choice (SAT-MC)The participant views animations of moving geometric figures and responds to questions about the meaning and motive of the figures’ movement. Japanese versions of both the SAT-MC I and II were newly prepared. The original English texts were translated to Japanese and then back-translated to English. The back-translations were reviewed by the original author and modifications were made to the Japanese translation as deemed necessary. The estimated time required is 10 min [29].Biological Motion Task (BM)The BM consists of two tasks that measure the ability to distinguish biological motion. In the first task, the participant distinguishes between human movement and scrambled (nonbiological) motion represented by point-lights. In the second task, scattered moving point-lights are projected onto human movement and scrambled motion, and the participant is asked to distinguish between them. The number of scattered moving point-lights varies depending on the movement in each trial. The estimated time required is 10 min [30].

#### 2.3.4. Theory of Mind

Hinting Task (Hinting)The participant reads and hears a dialogue between two characters and identifies the true intention behind one character’s indirect speech. A new Japanese version was prepared with permission from the original author. In this new version, in order for the participant to take the test by themself on a computer, they answer each question twice, first without a hint, and then with a hint. The participant answers the questions aloud and these answers are recorded. Based on the recording, 2 points are given for correct answers in the no-hint phase, 1 point for correct answers in the hint phase, and 0 points for not answering any of the questions correctly. The estimated time required is 6 min [31].Metaphor and Sarcasm Scenario Test (MSST)The participant reads 10 passages involving metaphors and sarcasm and chooses the answer that most accurately describes the passage. The estimated time required is 8 min [32].

### 2.4. Other Measurements

Background informationInformation such as sex, age, educational background, medical history, treatment history, primary disease, history of allergies, and history of side effects will be collected from medical records or interviews with participants.Mini-International Neuropsychiatric Interview (M.I.N.I.)The M.I.N.I is a structured interview designed to diagnose mental disorders. The present study uses the version of the M.I.N.I adapted to the DSM-V. The M.I.N.I will be conducted after obtaining informed consent to confirm history of mental disorders in healthy participants. For participants with schizophrenia, the M.I.N.I. will be performed after obtaining consent to determine whether they meet the inclusion criteria. The interview will take roughly 30 min [33,34].Japanese Adult Reading Test-25 (JART-25)The JART-25, a measure of verbal IQ, consists of 25 two-character kanji compound words that participants are asked to read aloud. In patients with schizophrenia, the JART-25 is considered to reflect premorbid verbal IQ. The estimated time required is 5 min [35].Positive and Negative Syndrome Scale (PANSS)The PANSS assesses overall psychiatric symptoms in schizophrenia via interview. The scale is composed of 30 items: 7 items on positive symptoms, 7 items on negative symptoms, and 16 items on general psychopathology symptoms. This study will use the Japanese version of the PANSS, which was translated by the Japan Young Psychiatrists Organization. The estimated time required is 30 min. Assessment by an informant (estimated time required: 10 min) is also performed [36,37].Brief Negative Symptom Scale (BNSS)The BNSS is a 13-item scale that assesses negative symptoms in schizophrenia via interview. The estimated time required is 15 min [38,39].Defeatist Performance Beliefs (DPB) ScaleThe DPB Scale is a self-administered scale for assessing negative beliefs about oneself. The estimated time required is 5 min [40,41].General Causality Orientations Scale (GCOS)The GCOS is a self-administered scale that assesses individual tendencies regarding three different motivational orientations (autonomy, control, and impersonal, which correspond to intrinsic motivation, extrinsic motivation, and amotivation, respectively). The estimated time required is 10 min [42].Self-Assessment of Social Cognition Impairments (ACSo)The ACSo is a 12-item self-administered questionnaire that examines subjective complaints regarding four different domains of social cognitive impairment. The estimated time required is 5 min [43,44]. The original French text was translated to Japanese and then back-translated to French. The back-translation was reviewed by the original authors and modifications were made to the Japanese translation as deemed necessary.Observable Social Cognition Rating Scale (OSCARS)The OSCARS is an 8-item scale that comprehensively examines subjective complaints regarding social cognitive impairment. The scale involves a self-report and an objective assessment from an informant close to the participant. The estimated time required is 5 min [45,46]. The original English text was translated to Japanese and then back-translated to English. The back-translations were reviewed by the original authors and modifications were made to the Japanese translation as deemed necessary.Brief Assessment of Cognition for Schizophrenia, Japanese Version (BACS-J)The BACS, which is a standardized test battery for which validity has been examined, was developed to assess cognitive impairment in schizophrenia. The assessment, which is currently widely used for psychiatric disorders, consists of verbal memory, working memory, motor speed, attention, verbal fluency, and executive functions. The estimated time required is 30 min [47,48].University of California, San Diego Performance-based Skill Assessment—Brief (UPSA-B)The UPSA-B measures functioning in two domains: financial management and communication (by telephone), in a role-playing scenario that models daily living. The estimated time required is 10 min [49,50].Specific Levels of Functioning Scale (SLOF)The SLOF objectively assesses social functioning by integrating the results of interviews with the participant and a close informant with results from a self-administered questionnaire. The estimated time required is 10 min [51,52].Gut microbiotaUsing a specialized gut microbiota measurement kit, we will measure gut microbiota as described previously [53,54]. Based on reference sequences, we will categorize bacteria into operational taxonomic units and calculate the occupancy rate (the percentage of the gut microbiome occupied by a given bacterium) of each bacterium at the genus level.

### 2.5. Sample Size Calculation

The present study aims to simultaneously assess measures of social cognition and quantitatively determine which measures are psychometrically superior. We will calculate various psychometric indicators with an emphasis on whether they can independently predict social functioning; specifically, we will emphasize the incremental validity of social functioning (defined as a significant increase in the coefficient of determination when social functioning testing is added after neurocognitive function testing has been included in advance as an independent variable) as determined by hierarchical multiple regression analysis. Sample size was calculated based on hierarchical multiple regression analysis.

In multiple regression analysis, f^2^ indicates effect size. According to Cohen [55], f^2^ values of 0.02, 0.15, and 0.35 represent small, moderate, and large effect sizes, respectively. In the present study, Model 1 uses the six cognitive domains assessed by the BACS-J (verbal memory, working memory, motor speed, attention, verbal fluency, and executive function) as explanatory variables and social functioning (SLOF and UPSA) as the response variable. In Model 2, each of the social cognition measures is added one at a time. Based on a previous study [7], the effect size of Model 1 is assumed to be 0.25, which is halfway between moderate and large. The present study requires a sample size sufficient to give an increase in the effect size of Model 2 to large (0.35), that is, to detect social cognition measures that, when added, boost the predictive ability of social functioning from halfway between moderate and large. The sample size necessary for detection with α = 0.05 and β = 0.2 is 99 participants (SAS 9.4). To conduct this analysis, all measures must be completed. In view of the high dropout rate of 40% in a previous study [7], we assumed a dropout rate (dropping out at any time before the final analysis) of 30% in the present study; therefore, we set the target sample size at 140 participants.

The purpose of recruiting healthy individuals for this study is to estimate reference values for social cognition measures in the general population in an exploratory fashion. We will recruit 8 participants in each of eight classifications (men and women in their 20s, 30s, 40s, and 50s). In consideration of dropouts, we set the target sample size at 70 participants.

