### 2.6. Statistical Methods

For participants’ background information, we will calculate summary statistics separately for the patient group and the healthy group and compare them between groups. To examine the relative merits of social cognition measures, we will calculate the following psychometric indicators. For reliability, in addition to performing correlation analysis and assessing test–retest reliability, we will calculate Cronbach’s alpha to assess internal consistency. For changes from the initial test to the retest (learning effect), we will calculate Cohen’s d and state the respective frequencies of floor/ceiling effects. In addition to performing simple correlation analysis for each social cognition test and social functioning, we will perform multiple regression analysis to determine the overall extent to which each of the social cognition measures predicts social functioning. For each social cognition measure, we will also examine the incremental validity of social functioning (defined as a significant increase in the coefficient of determination when social functioning testing is added after neurocognitive function testing has been included in advance as an independent variable) as determined by hierarchical multiple regression analysis. Furthermore, we will calculate the means and standard deviations (SDs) for the time required for each social cognition measure and participants’ subjective assessments of each measure separately for the patient group and the healthy group. We will also calculate means and SDs of results for each social cognition measure separately for the patient group and the healthy group, compare means between the two groups, and note Cohen’s d.

The details of the above statistical analysis will be shown separately in a statistical analysis protocol that will be drafted by the time final data entry is closed. Interim analysis will not be conducted. For missing data, we are considering listwise deletion as the first option. However, if listwise deletion results in a high percentage of missing data, we will consider statistical analysis that imputes missing data.

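### The stated aim is to find which measures are superior, but the emphasised indicator gives each measure its own significance verdict and never compares measures

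*Protocol article*

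**What the plan says.** Section 2.5 sets the goal as a ranking: to "quantitatively determine which measures are psychometrically superior". It continues: "We will calculate various psychometric indicators with an emphasis on whether they can independently predict social functioning". The emphasised indicator is incremental validity, which Sections 2.5 and 2.6 both define by significance ("defined as a significant increase in the coefficient of determination").

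Model 1 holds the "six cognitive domains assessed by the BACS-J", with "social functioning (SLOF and UPSA) as the response variable". In Model 2, "each of the social cognition measures is added one at a time". The required 99 evaluable patients are derived from this single-measure step at α = 0.05 and 80% power. Eight measures are to be judged: "Of the nine tests recommended by the panel, the Penn Emotion Recognition Task (ER-40) [23] was excluded", and Section 2.3 describes the remaining eight.

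Section 2.6 lists further indicators of relative merit: test-retest reliability, internal consistency, learning effect, floor and ceiling effects, correlation with functioning, administration time, subjective burden and patient-healthy differences. Section 4.1 has an expert panel vote a three-level grade for each measure, drawing on these results and on criteria set in advance.

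**The concern.** Superiority is a statement about the difference between two measures. The emphasised indicator is a yes/no verdict for each measure taken alone against zero. The two questions differ. Two measures with nearly the same R² increase can fall on either side of p = 0.05, and two with quite different increases can both be significant. In neither case does the verdict say which is better.

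The stake is what reaches the panel. If the most emphasised validity result arrives as significant or not significant, the panel may treat a chance split as a difference in merit. All measures are taken in the same patients, so the data for a direct comparison will exist. The text does not describe using them that way.

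**Working it through.** **Inputs (Section 2.5 unless noted).** Model 1 f² = 0.25 ("the effect size of Model 1 is assumed to be 0.25"); Model 2 f² = 0.35; six Model 1 predictors and one added measure, so seven in Model 2; α = 0.05; N = 99. Number of measures: 9 − 1 = 8 (Section 2.1). The document gives no correlation between measures, so correlations of 0, 0.3 and 0.5 between test statistics are assumptions.

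**Step 1: the planned increment.** R² = f²/(1 + f²).
- Model 1: 0.25/1.25 = 0.200
- Model 2: 0.35/1.35 = 0.2593
- Increase: 0.0593
- Partial f² for the added measure: 0.0593/(1 − 0.2593) = 0.0593/0.7407 = 0.08

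**Step 2: reproduce the plan's figure.** Partial F test with 1 and 99 − 7 − 1 = 91 degrees of freedom and noncentrality λ = N × f² = 99 × 0.08 = 7.92. Power is 79.5%, and 80% is reached at N = 101 against the stated 99. The plan's figure is reproduced to within two patients. The 80% is therefore the power for one measure on one outcome.

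**Step 3: two equally good measures.** Both have true partial f² = 0.08, so each is significant with probability 0.795. If the tests are independent, the chance of opposite verdicts is 2 × 0.795 × (1 − 0.795) = 0.326, about 33%. With correlated statistics (bivariate normal, both means √7.92 = 2.81, critical value 1.984, simulated):

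| Assumed correlation | Opposite verdicts |
|---|---|
| 0 | 32% |
| 0.3 | 27% |
| 0.5 | 23% |

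The simulated 32% at zero correlation agrees with the exact calculation to within the normal approximation.

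**Step 4: eight equally good measures, one outcome.** If independent, the chance that at least one misses is 1 − 0.795⁸ = 0.84. By simulation it is 84%, 68% and 58% at correlations 0, 0.3 and 0.5. On average about 6.4 of the eight would be significant, so the usual picture is a minority of equally good measures left without the label.

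**Step 5: sensitivity.** Step 2 treats the predictors as fixed. With random predictors, simulated power at N = 99 is 75.9%, and independent disagreement rises to 2 × 0.759 × 0.241 = 0.366, about 37%. The figures in Steps 3 and 4 are therefore not at the pessimistic end.

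**Step 6: what the label hides.** With 98 evaluable patients (140 × 0.7), simulation puts the estimated increase for a true value of 0.059 anywhere from 0.004 to about 0.157. A yes/no verdict conceals that spread; an interval shows it.

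**The case against.** The strongest reply is that the plan does not decide merit by these p-values. Section 2.6 lists many indicators, most of them estimates. Section 4.1 leaves grading to a panel vote by intended use, with at least 80% consensus. It also describes incremental validity there as a further gain in predictive power, with no significance threshold. All of that stands. A reader might infer that superiority is to be read from significance alone, or that the label fixes the published grade; the documents do not support that.

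A reader might also infer 16 uncorrected tests, from eight measures on two outcomes. That is not established either. The response variable is written in the singular, so SLOF and UPSA could mean two models or one composite. The α of 0.05 is fixed only for sizing. Section 2.6 defers analysis details to a separate statistical analysis protocol, where multiplicity and an order of outcomes may properly be set. Family-wise control is in any case debatable when each measure is graded on its own and several may be recommended together. Making SLOF the sole criterion would likewise be a preference, since Section 2.5 names both scales.

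Deferral does not dispose of the remaining point. The definition by significance is written into both sections, and the later document is to give details of the analysis described there. The threshold-free wording in Section 4.1 does not withdraw that definition; it leaves two descriptions of the same indicator.

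**Conclusion.** The point holds in a limited form. The emphasised indicator, as defined, cannot answer the between-measure question that the study sets itself, and no comparison of increments is described. At the planned increment and N = 99, two equally good measures would be split by chance in about 23% to 33% of studies. At least one of eight equally good measures would miss in about 58% to 84%.

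These figures rest on the plan's own effect sizes, on a single outcome, and on assumed correlations of 0.5 down to 0 between test statistics. They describe the label, not the panel's final grade, to which the label is one of several inputs. This is a cheap improvement to the analysis text and not a flaw that invalidates the study.

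**What to change.** In Section 2.6:
- Define incremental validity by the size of the R² increase over the BACS-J model, and report it for each measure with a 95% bootstrap confidence interval.
- Add paired bootstrap confidence intervals for the difference in increase between measures, resampling the same patients for both.
- Apply the same analysis to SLOF and to UPSA-B as response variables, and say so.
- Give the panel these estimates and intervals in place of the significance label, and align the definition in Section 2.5.

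No additional patients, visits or tests are needed. The cost is a change of wording and a little more analysis. The downside is that, with about 99 patients, the intervals will be wide and may show that few measures can be separated. The study is not sized for such comparisons, and no sample size for them can be worked out from the document, because it gives neither an expected difference between measures nor their correlation.
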